#### 8.4 DATA COLLECTION TOOLS

Study instruments will include structured forms for clinical history, physical assessment, laboratory evaluations and information about expenses, resource and time use, with open-ended fields for unanticipated findings and place for comments. In addition there will be interview guides for In-depth Interviews and Focus Group Discussions. Prior to data collection these will be translated into Chichewa language and back-translated for accuracy. The forms will be administered to the participants in Chichewa which is the national language but also a common language in the study area.

#### 8.5 VARIABLES

The study will include a range of variables, identified both at the time of enrolment and at follow-up. Demographic information on children including age, sex, religion, village of residence and socioeconomic features of household will be collected, as well as cost information for the economic evaluation. Information to assess the acceptability of PMC, adaptations to health workers' working practices required to implement PMC, perceptions of the feasibility of implementing PMC through different delivery mechanisms, and recommendations on effective implementation will also be collected. Clinical information collected on history of current and previous illnesses and hospital admissions will be collected in addition to hospitalisations and mortality. For children who are hospitalized during the follow-up period, data will be collected on the length of hospitalization, diagnosis, treatments provided, laboratory results, and participant outcome. Physical exam and laboratory test results collected will include: height, weight, Mid Upper Arm Circumference (MUAC), Malaria rapid testing (mRDT) results, blood slide results, parasitaemia level, and haemoglobin level.

#### 8.6 TRIAL MEDICATION AND INTERVENTIONS

##### 8.6.1 Study Medications

###### 8.6.1.1 Dihydroartemisinin-piperaquine

We shall use the GMP formulation of Dihydroartemisinin-piperaquine (DHA): Eurartesim®, a GMP certified product from Sigma Tau and approved by the European Medicines Agency (EMA) in October 2011. Eurartesim is a co-formulated tablet containing 40 mg dihydroartemisinin and 320 mg piperaquine phosphate or as 20/180 (paediatric formulation).

Dosing will be by bodyweight according to the following schedule recommended by the manufacturer (

**Table 4:** Dihydroartemisinin-piperaquine (Eurartesim®) weight-based dosing schedule

---

). WHO is in the process of revising the dose recommendations for DP in this age group. We will utilize the new dose recommendations as soon as WHO will make these available.

**Table 4:** Dihydroartemisinin-piperaquine (Eurartesim®) weight-based dosing schedule

| Weight in Kg        | Daily dose (mg) |     | Tablet strength and number of tablets per dose |
|---------------------|-----------------|-----|------------------------------------------------|
|                     | Piperaquine     | DHA |                                                |
| 5 to <7   | 80              | 10  | ½ x 160 mg / 200 mg tablet                     |
| 7 to <13  | 160             | 20  | 1 x 160 mg / 200 mg tablet                     |
| 13 to <24 | 320             | 40  | 1 x 320 mg / 400 mg tablet                     |
| 24 to <36 | 640             | 80  | 2 x 320 mg / 400 mg tablet                     |

*If the paediatric strength tablets are not available, the full tablet strength can be used to provide the equivalent dose in mg (i.e. ¼ tablet and ½ tablet of 320 / 40 mg tablets for the first two weight bands)*

### 8.6.2 Drug administration

For all the OPD arms, the first dose will be given as a crushed powder mixed with water at the OPD. The remaining two doses will be given to take at home during the following two consecutive days. Participants in other study arms will take all the drugs at home. Participants will be advised to give the drug to the child at about the same time each day with water. Should a caretaker forget to give the drug dose at the set time, they will be advised to take it as soon as realised and to continue the recommended regimen until the dose is completed.

Participants who take the Eurartesim at the OPD will be observed for 60 minutes. Should a participant vomit within 30 minutes of receiving the treatment drug, the full dose will be re-administered. Should a participant vomit within 30-60 minutes of drug intake, half dose will be re-administered.

To minimise QTc prolongation, the manufacturer of Eurartesim advises patients to take the first day's dose approximately three hours after meals as fatty food can increase the absorption of piperaquine. However, overall studies show that DP is well tolerated and can be given with small amount of food, although trough drug levels are also effective when given to fasting patients.

#### 8.6.2.1 Artemether lumefantrine

Although not part of the study drugs, Good manufacturing Practice (GMP) formulation of Artemether Lumefantrine: Coartem, Novartis Pharmaceuticals will be administered to all study participants in hospital as part of standard care. AL will be dosed along with a small amount of food, e.g. a biscuit. The recommended treatment is a 6-dose regimen over a 3-day period. The standard tablet or the dispersible tablets containing 20mg of artemether and 120mg of lumefantrine will be used and dosed according to body weight as per WHO dosing recommendation as provided in the latest WHO malaria treatment

guidelines. The dose regimen will be updated if and when WHO updates their dose recommendations. The dosing is based on the number of tablets per dose according to pre-defined weight bands and the current recommendations are:

| Body Weight | Recommended number of AL tablets |
|--------------------|-----------------------------------------|
| 5-14 kg            | 1 tablet                                |
| 15-24 kg           | 2 tablets                               |
| 25-34 kg           | 3 tablets                               |
| > 34 kg            | 4 tablets                               |

These doses are given twice a day for 3 days. This extrapolates to 1.7/12 mg//12-mg/kg body weight of artemether and lumefantrine, respectively, per dose, given twice a day for 3 days with a therapeutic dose range of 1.4-4 mg/kg of artemether and 10-16 mg/kg of lumefantrine.

**Table 3:** Artemether Lumefantrine weight based dosing schedule

| Weight in Kg | Number of pediatric tablets of Coartem® per dose |         |              |          |              |          |
|---------------------|---------------------------------------------------------|---------|--------------|----------|--------------|----------|
|                     | Day 1                                            |         | Day 2 |          | Day 3 |          |
|                     | 1 st dose                                    | 8 hours | 24 hours     | 36 house | 48 hours     | 60 hours |
| 5 to <15  | 1                                                       | 1       | 1            | 1        | 1            | 1        |
| 15 to <25 | 2                                                       | 2       | 2            | 2        | 2            | 2        |
| 25 to ≤34    | 3                                                       | 3       | 3            | 3        | 3            | 3        |
| >34       | 4                                                       | 4       | 4            | 4        | 4            | 4        |

### 8.6.3 Information on how to give study drugs at home

Participants in all the five arms will take the drug at about the same time each day. Should mother/guardian forget to give the child the drug dose at the set time, they will be advised to give it as soon as realised and to continue the recommended regimen until the treatment is completed. The mother/guardian will be advised to observe participants for 60 minutes after taking DHP. Should a participant vomit within 30 minutes of receiving the treatment drug, the mother/guardian is instructed to re-administer the full dose. Should a participant vomit within 30-60 minutes of drug intake, half dose will be re-administered. Repeat dosing will be attempted once.

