| Location                    | In-Hospital             |                               |                                  | Clinic                    | Home/OPD                                               |                                     |                                      |                          |          |          |           |           |           | Clinic            |
| Visit number                | Pre-study Screening     | Screening Consent & Base-line | #1
t=0 weeks;
Allocation   | #2
t=2 weeks;
DHP 1 | #3
t=6 weeks
DHP 2                               | #4
t=10 weeks
DHP 3           | #5
Study end visit                | 14 wks
(day 98 +/- 7) |          |          |           |           |           |                   |
| Visit description           |                         |                               |                                  |                           |                                                        |                                     |                                      |                          |          |          |           |           |           |                   |
| Study Time                  |                         |                               |                                  |                           |                                                        |                                     |                                      |                          |          |          |           |           |           |                   |
|                             | Days -4 a -0 | Day0                          |                                  |                           | 2 weeks (day 14 +/- 3) c                    | 6 weeks (day 42 +/- 4) c | 10 weeks (day 70 +/- 4) c |                          |          |          |           |           |           |                   |
|                             |                         |                               |                                  |                           | 2w- Day 1                                              | 2w- Day2                            | 2w- Day3                             | 6w- Day1                 | 6w- Day2 | 6w- Day3 | 10w- Day1 | 10w- Day2 | 10w- Day3 |                   |

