|                                            |                         |                               |                       |                                                                                                                                                                           | X        | X        | X                    |          | X        | X                       | X         |           |                       |
| Patient costs                              |                         |                               | X                     |                                                                                                                                                                           |          |          |                      |          |          |                         |           |           | X                     |

Visit #1: Enrolment and randomisation at discharge

Visit #2 #3#4: Home visits at 6, 10 and 14 weeks after enrolment to assess uptake of the 1st, 2nd and 3rd treatment course of the PMC study drugs respectively.

Visit #5: at 3.5 months after enrolment. This is the close out assessment.

---

- a. Children can be pre-study screened any time between hospital admission and enrolment. The figure of -4 days is provided for illustration purposes only.
- b. Visit window= number of days an actual subject visit may fall outside of the planned protocol schedule visit to still meet protocol requirements. DP should be given at least 4 weeks apart.
- c. MS, malaria smear. This will be collected for research purposes only, and read days to weeks later. Malaria smears will not be used for point of care. If participants are symptomatic (e.g. fever) an RDT will be taken for point of care.
- d. VP=vena puncture. FP=finger prick, DP=dihydroartemisinin-piperaquine, , Hb=haemoglobin, MS=malaria smear, Pf=Plasmodium falciparum

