#### 8.1.1 Rationale for the trial arms

There is need to assess a number of strategies for effective delivery of PMC in a largely rural community that would typically benefit from this intervention. Presently in African health systems and particularly Malawi there is no post-discharge health management system. Most patients once discharged are no longer expected to have contact with the health system apart from for EPI visits (if less than 9 months old). Post-discharge health care becomes very important in severe anaemia as it has been shown that they are at particular risk of dying or having another episode of severe anaemia.

We postulate that this post-discharge care in the form of PMC may be delivered either in the community or at a health facility. The most likely scenario where the health care provider is least involved would be where mothers are given PMC drugs on discharge from hospital and allowed to administer the drugs on her own to the child ([Arm 1](#)). However as we postulate that the mother could forget to administer the PMC, we would like to test a number of reminder systems. The first is through the use of SMS technology, which has been shown to be user friendly and acceptable from our own pilot work and other programs in Malawi that are currently using it ([Arm 2](#)). FrontlineSMS™ is a simple and free desktop software that enables instantaneous 2-way communication to any mobile handset. It is easy to implement, simple to operate and the only cost is for the sms that is sent ([www.frontlinesms.com](http://www.frontlinesms.com)).

An alternate reminder system is the use of HSA. HSA are Ministry of Health (MoH) employees who are responsible for basic health promotion activities in the community. Ideally MoH strives to have 1 HSA for every 1000 people, but in reality they often cater for much larger populations. As they are the main MoH community health workers they are usually over burdened with many disease control programs. In some areas in rural Malawi there are Village Health committees, which are made up of voluntary members of the community. They work hand in hand with the HSA. We postulate that HSAs and where available village health volunteers (VHVs) are an option for reminding mothers to give PMC to their child ([Arm 3](#)).

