#### 8.7.6 **Adherence to study intervention protocol and strategies for retention**

##### 8.7.6.1 Adherence to study protocol and medication

At 2, 6 and 10 weeks mothers will be asked to administer already received PMC drug or asked to come to the clinic to receive the drugs. At discharge all mothers regardless of the arm they have been randomised to will be instructed on how to administer DHA to their child. Nurses will demonstrate this by using dummy tablets (placebos) and later the mothers will be asked to do it under supervision. Mothers will be given adequate time to ask for any clarifications during this process. Mothers will also be informed to report to the hospital for any adverse events that the child might experience whether they suspect they are related or not to the study drug.

At discharge, after randomisation, all mothers will be informed of the dates for PMC. These dates will be written in the child's Health Passport and they will additionally be provided with a laminated study card which will contain the Study ID of the child, Name of the child and PMC-1, PMC-2 and PMC-3 dates.

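### The open-ended instruction on forgotten doses, the course dates fixed at discharge and the 4-week minimum between courses are not consistent, so a home course started late can breach the protocol's own minimum

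*Protocol*

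**What the plan says.** Four parts of the protocol bear on the spacing of courses.

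- **Forgotten doses.** Section 8.6.3 covers the case "Should mother/guardian forget to give the child the drug dose at the set time" and says of carers that "they will be advised to give it as soon as realised and to continue the recommended regimen until the treatment is completed". Section 8.6.2 gives nearly the same advice: "they will be advised to take it as soon as realised and to continue the recommended regimen until the dose is completed". Neither section states a cut-off or says what happens to the next course.
- **Minimum spacing.** Note b to Table 2 (section 4.2) states: "DP should be given at least 4 weeks apart". It does not say whether this runs from start to start or from the last dose to the next first dose.
- **Planned days.** Table 2 places the courses at day 14 (window 3 days either side), day 42 (4 days) and day 70 (4 days). Note b defines the window for visits. The carer instructions mention neither the windows nor the minimum.
- **Dates given to the carer.** Under section 8.7.6.1, the dates go into the Health Passport at discharge and onto "a laminated study card which will contain the Study ID of the child, Name of the child and PMC-1, PMC-2 and PMC-3 dates". Section 8.1 ties the SMS and HSA reminders to each due date. No passage describes changing a later date after a late course.

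In Arms 1-3 the carer leaves hospital with the drugs for all three courses (8.1). In Arms 4-5 the first dose of each course is given at the OPD (8.6.2).

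**The concern.** Forgetting is the event that the reminder arms are designed to address: section 8.1.1 says "we postulate that the mother could forget to administer the PMC". The instruction on forgotten doses is therefore not a rarely used clause. A carer in Arms 1-3 who starts a course late, completes it as told and begins the next on the card date has done everything asked of her, yet the interval is shorter than the protocol's minimum. No staff contact is required before she starts that next course.

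Specific objective 3 (7.2) compares the safety of community and facility delivery. Section 14.5.4 names dose-dependent QTc prolongation as the main safety concern with piperaquine, while describing it as mild, with no clinical signal of significant arrhythmia. If short intervals arise at different rates by arm, they become part of that safety comparison, and the protocol has no stated requirement to tabulate them.

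**Working it through.** **Inputs.** Planned starts on days 14, 42 and 70 and windows of 3, 4 and 4 days (Table 2, first part; its repeated header carries a different day for week 6, but day 42 agrees with 6 weeks). Minimum interval 4 weeks = 28 days (note b). Courses of 3 daily doses.

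**1. Planned spacing.** 42 - 14 = 28 and 70 - 42 = 28. The schedule meets the minimum exactly; the slack is 28 - 28 = 0 days.

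**2. First dose L days late, next course on its printed date.** Start-to-start interval = 28 - L.

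| L (days) | Interval (days) |
|---|---|
| 0 | 28 |
| 1 | 27 |
| 3 | 25 |
| 4 | 24 |
| 7 | 21 |

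Any delay of a day or more takes the interval below 28. The values of L are illustrative.

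**3. Delay at the upper edge of the window, next course on its printed date.** Course 1 to 2: 42 - (14 + 3) = 25 days. Course 2 to 3: 70 - (42 + 4) = 24 days. Staying within the window does not keep the interval at the minimum.

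**4. Only the second or third dose late.** The first dose is still on its planned day, so the start-to-start interval stays at 28 days.

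**5. The other reading of note b.** Counted from the last dose to the next first dose, an entirely on-time schedule gives 42 - 16 = 26 days. That reading fails with no forgotten dose at all, so the check uses start-to-start.

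**6. The windows alone.** Late edge to early edge: (42 - 4) - (14 + 3) = 38 - 17 = 21 days, and (70 - 4) - (42 + 4) = 66 - 46 = 20 days. Table 2 thus conflicts with its own note even without a forgotten dose. This is a related problem that the same repair should cover.

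**The case against.** The strongest reply is that the instruction concerns daily doses within a 3-day course. Section 8.6.3 speaks of giving the drug at about the same time each day and then of a dose missed at its set time; it is not written as a rule for starting a whole course late. Much of this stands: lateness of some hours, or a late second or third dose, leaves the interval at 28 days. But the first dose also has a set time, and neither section exempts it.

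A second reply is that the protocol nowhere says the dates cannot be moved, and that note b, read with the windows, could let staff shift a course. That also stands, and it is why the instructions can lead to a breach but need not. It does not help a carer in Arms 1-3 who holds the drugs and a card with three dates and has not been told of the minimum.

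Three stronger readings are tempting, and the documents do not support them.

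- **That lateness in the home arms would go unseen.** Section 8.9.1 provides unannounced spot checks on day 4 or 5 of each course, with a pill count and an interview, and its questionnaire asks whether and when dosing took place. Section 8.12.1 speaks of visits to a subset, so coverage is not certain, but timing is a stated item.
- **That the OPD arms are protected.** Dispensing dates are logged (8.6.4.5), but no passage tells OPD staff to check the interval before giving a course.
- **That about half of Arm 1 would be affected**, since section 8.3 assumes 50% uptake without SMS. The remainder includes doses never given, and a course completed late might still count as uptake. The assumption therefore says nothing about the share started late. Section 8.3 also assumes the same 50% for OPD and home delivery, so it gives no ground for expecting more late courses at home. Delays of several weeks likewise have no basis in the text.

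**Conclusion.** The concern holds as an inconsistency between stated rules. The schedule has zero slack against the 28-day minimum. A first dose given a day or more late, followed by the next course on its printed date, therefore gives an interval of 28 - L days, and 25 or 24 days at the upper edge of the window. This assumes that note b is counted start to start, that the first dose is the one delayed, and that the carer keeps to the card date. How often these conditions coincide cannot be worked out from the protocol. The point deserves correction because the collision arises in the behaviour under study and the repair is cheap. It does not show that short intervals will be common, or that they would be harmful.

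**What to change.** Reconcile sections 8.6.2, 8.6.3 and 8.7.6.1 and the Table 2 windows with note b, so that one consistent instruction on a late course and on the course after it reaches carers in all five arms. State in note b how the 4 weeks are counted. The clinical content of the instruction is for the investigators and safety monitor to settle.

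Record the actual date of each dose at the existing spot checks and OPD visits, and report start-to-start intervals under 28 days by arm alongside the safety outcomes.

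The cost is rewording of the card and the carer training, and one date field per dose on forms already completed at those contacts. Part of that information may already be captured by the spot-check questionnaire and the dispensing log.

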#### 8.6.4 Procedures for Drug handling & Accountability

##### 8.6.4.1 Preparation and packaging

All subject-specific study drugs will be prepared and stored in small opaque medicinal containers provided by the sponsor, according to the subject's body weight recorded at enrolment. This will be done by the pharmacy Assistant. Prior to each drug administration, the drugs will be crushed and suspended in the opaque container by adding flavoured syrup.

